### 8.2 Data entry/ EDC

An EDC system will be provided. The EDC system will consist of an android module and a web module. The android module will be pre-installed on tablets that will be distributed to the sites. The web module will be used for data processing and management by INCLEN and P95. The software will be developed using open source (PHP and MySQL). Sites will be provided with comprehensive training on the use of the EDC system, including eCRF completion guidelines.

User testing will be performed prior to deployment (see 8.1). The data collection tool functionality will be based on the CRFs.

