## Neonatal infection

| Neonatal invasive blood stream infections: bacterial/fungal/viral.                                                                                                                                                                                                                                                                                                                                                                                                                                                                                                                                                                                                                                                                                                                                                                                                                                                                                                                                                                                                                       |                                                                                                                                                                                                                                                                                                                                                                                                                                                                                                                                                                                                                                                                                                                                                                                                                                                                                                                                                                                                             |                                                                                                                                                                                                                                                                                                                                                                                                                                                                             |

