| 
Recognised pathogena identified using a validated method and from a normally sterile siteb
 
If an organism normally considered non-pathogenic is isolated from blood culturesa: Level 1 requires its identification from at least 2 blood cultures taken from two different sites, or at 2 different times, PLUS 1 of the criteria as per level 2 of evidence
                                                                                                                                                                                                                                                                                                                                                                                                                                                                                                                                                                                                                                                                              | 
Not meeting Level 1 of evidence
 
AND
 
3 or more criteria:
 
 
• Temperature <math>\geq 37.5^{\circ}\text{C}</math> or <math>< 35.5^{\circ}\text{C}</math>f
 
• Tachycardiad or new or more frequent episodes of bradycardiad
 
• New or more frequent episodes of apnead or increased oxygen requirement or increased requirement for ventilatory support
 
• Lethargy or moving only when stimulated or hypotonia or irritability
 
• Difficulty in feeding or abdominal distention
 
• Pallor or poor perfusiond or hypotensiond
 
• Abnormal White Cell Countd or I/T ratio <math>> 0.2</math>
 
• Abnormal platelet countd
 
• Increasede inflammatory markers (CRP, procalcitonin)
 
• Metabolic acidosis as defined by a base excess (BE)d
 
 | 
Not meeting Level 1 or 2 of evidence
 
AND
 
2 or more of the following criteria:
 
 
• Temperature <math>\geq 37.5^{\circ}\text{C}</math> or <math>< 35.5^{\circ}\text{C}</math>f
 
• Tachypnead or severe chest indrawing or grunting or cyanosis
 
• Change in level of activity
 
• History of feeding difficulty
 
• History of convulsions
 
 |

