| 
Recognised pathogena identified using a validated method from cerebrospinal fluid (CSF)
 
If an organism normally considered non-pathogenic is identified from the CSF, LEVEL 1 of evidence additionally requires all LEVEL 2 criteria: i.e. CSF pleocytosis AND temperature criteria AND 1 or more clinical criteria
                                                                                                                                                                                                                 | 
CSF pleocytosisd OR positive IgM antibodies to a specific pathogen in the CSF
 
AND
 
Recognised pathogena identified using a validated method from a normally sterile siteb (other than CSF)
 
AND
 
Temperature <math>\geq 37.5^{\circ}\text{C}</math> or <math>< 35.5^{\circ}\text{C}</math>c
 
AND
 
1 or more criteria:
 
 
• History of convulsions
 
• Lethargy or irritability
 
• Coma
 
• Apnead
 
• Bulging fontanel
 
• Neck stiffness
 
 | 
CSF pleocytosisd
 
AND
 
NO d pathogena identified using a validated method from a normally sterile siteb
 
AND
 
Temperature <math>\geq 37.5^{\circ}\text{C}</math> or <math>< 35.5^{\circ}\text{C}</math>c
 
AND
 
3 or more criteria:
 
 
• History of convulsions
 
• Lethargy or irritability
 
• Coma
 
• Apnead
 
• Bulging fontanel
 
• Neck stiffness
 
 | 
No lumbar puncture done or no sample available
 
AND
 
Temperature <math>\geq 37.5^{\circ}\text{C}</math> or <math>< 35.5^{\circ}\text{C}</math>c
 
AND
 
4 or more criteria:
 
 
• History of convulsions
 
• Lethargy or irritability
 
• Coma
 
• Apnead
 
• Bulging fontanel
 
• Neck stiffness
 
 |

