| 1                                                                                           | Date of birth of the newborn                                                                                                                                                                       | Please enter DDMMYYYY or unknown. |
| B Date of onset and diagnosis                                                        |                                                                                                                                                                                                    |                                          |
| 2                                                                                           | What was the date of the first sign/symptom of the neonatal bloodstream infection?                                                                                                                 | Please enter DDMMYYYY or unknown. |
| 3                                                                                           | What was the date of diagnosis?                                                                                                                                                                    | Please enter DDMMYYYY or unknown. |
| C Sample                                                                             |                                                                                                                                                                                                    |                                          |
| 4a                                                                                          | Were any samples from a normally sterile site tested for the presence of bacteria? Sterile sites are: blood, sterile urine (catheter urine or supra-pubic aspirate), pleural fluid, ascitic | Yes
No
Unknown                     |

|                                                                                                                  |                                                                                                              |                                                                                                                                                                          |

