|------------------------------------------------------------------------------------------------------------------|--------------------------------------------------------------------------------------------------------------|--------------------------------------------------------------------------------------------------------------------------------------------------------------------------|
| fluid, broncho-alveolar lavage, bone biopsy, synovial fluid.
(If 'no' or 'unknown', skip to section D) |                                                                                                              |                                                                                                                                                                          |
| 4b                                                                                                               | Was a pathogen found to be present in at least one of the samples? (If 'no' or 'unknown', skip to section D) | Yes
No
Unknown                                                                                                                                                     |
| Please fill in the question below for the first sample in which a pathogen was found.              |                                                                                                              |                                                                                                                                                                          |
| 5a                                                                                                               | What was the sample?                                                                                         | Ascitic fluid
Blood
Bone biopsy
Broncho-alveolar lavage
Pleural fluid
Sterile urine (catheter urine or supra-pubic aspirate)
Synovial fluid
Unknown |
| 5b                                                                                                               | Date sample was taken                                                                                        |                                                                                                                                                                          |

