| C Cerebrospinal fluid sample                                                                 |                                                                               |                                          |
| 4                                                                                                   | Was an cerebrospinal fluid (CSF) sample tested for the presence of pathogens? | Yes
No
Unknown                     |
| 5a                                                                                                  | Was a pathogen found to be present in at least one of the samples?            | Yes
No
Unknown                     |
| Please fill in the question below for the first sample in which a pathogen was found. |                                                                               |                                          |

|                                                                                                     |                                                                                                                                                                                                                                                                                                                                                |                                                                                                                                                                          |
|-----------------------------------------------------------------------------------------------------|------------------------------------------------------------------------------------------------------------------------------------------------------------------------------------------------------------------------------------------------------------------------------------------------------------------------------------------------|--------------------------------------------------------------------------------------------------------------------------------------------------------------------------|

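### Bloodstream infection form: the sample block opens only for bacterial testing, so a case tested only for virus or fungus cannot reach Level 1; two smaller gaps affect same-day cultures and meningitis Level 3b

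*Protocol*

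**What the plan says.** **Bloodstream infection, definition (Protocol, Annex III, Neonatal infection).** The heading reads "Neonatal invasive blood stream infections: bacterial/fungal/viral". Level 1 has two routes. The main one needs a recognised pathogen "identified using a validated method and from a normally sterile site". For an organism normally considered non-pathogenic, "Level 1 requires its identification from at least 2 blood cultures taken from two different sites, or at 2 different times", plus one Level 2 criterion.

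**Bloodstream infection, form (Protocol, Annex V).** Item 4a asks "Were any samples from a normally sterile site tested for the presence of bacteria"; No or Unknown sends the user past the sample items to the clinical criteria. Item 4b asks whether a pathogen was found. For each positive sample the form then takes specimen type (5a), "Date sample was taken" (5b), method (5c), organism class (bacteria, fungi, protozoa or virus) and organism name (5d). Organisms are sorted automatically into pathogenic and non-pathogenic, and further positive samples can be added with the same questions.

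**Meningitis (Annexes III and V).** The entry condition for Level 3b is "No lumbar puncture done or no sample available". Item 4 of the form asks "Was an cerebrospinal fluid (CSF) sample tested for the presence of pathogens". Items 8b and 8c ask about CSF pleocytosis and CSF IgM, each with Yes, No, or a combined unknown/not-measured answer.

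**Use of the forms.** Section 8.2 states: "The data collection tool functionality will be based on the CRFs". It also provides for programmed skip patterns. Section 4.10 assigns levels with an automated tool, and Section 5.5 analyses the data as entered, without imputation.

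**The concern.** The study tests whether sites can apply the GAIA definitions. A case that fails a level should therefore fail because of the site's records or the definition, and not because the form never asked. Item 4a is narrower than the definition it serves and controls access to every microbiological item. A site that answers it truthfully for a sample sent only for viral or fungal testing cannot enter the organism at all.

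The consequence is mainly for secondary outcome 1 (Section 5.3.1.1), the distribution by level. The exploratory tables are touched as well. A case left unclassified enters the table in Section 5.4.1, and one left at Level 3 enters the table in Section 5.4.2. In both, a gap in the form would look like a gap at the site. Primary applicability (Section 5.2.2.1) counts a case classified at any level, so it moves only when a case drops out of classification altogether or is classified wrongly.

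**Working it through.** No arithmetic applies. The check traces each criterion to the form items that should supply it.

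| Route in Annex III | Form items | Can it be established? |
|---|---|---|
| Bloodstream Level 1, recognised pathogen, sample tested for bacteria (alone or with other organisms) | 4a Yes, 4b, 5a–5d | Yes (method is recorded; whether it was validated is not) |
| Bloodstream Level 1, sample tested only for virus or fungus | 4a No, block skipped | No, as 4a is worded |
| Bloodstream Level 1, normally non-pathogenic organism, two blood cultures on different dates | 5a, 5b, repeat block | Yes; different dates are different times |
| Same, both cultures on one date | 5a, 5b, repeat block | No; there is no clock time and no draw site |
| Meningitis Level 3b, entry condition | 4, 8b, 8c | By inference only |

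**Item 4a against its surroundings.** The definition names three classes of organism, the organism-class item on the same form names four, and item 4a names one. The corresponding questions on the respiratory form (item 8) and the meningitis form (items 4 and 6) say pathogens. This looks like a drafting slip in 4a.

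**Where a case goes after losing Level 1.** Level 2 needs at least three of ten criteria and Level 3 at least two of five. These are collected in items 6a–6y. A viral or fungal case with enough recorded signs is still classified, at a lower level. With too few, it is unclassified.

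**Two-culture rule.** The rule is satisfied by different sites or by different times. Item 5a records the type of specimen (for example, blood), which is not the place on the body where it was drawn. Item 5b records a date. A pair on one date therefore cannot be tested against either limb.

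**Level 3b.** The temperature criterion (8d) and the six clinical criteria (8e–8j) are all collected. Only the entry condition lacks a direct item:
- Yes to item 4, 8b or 8c shows that CSF was obtained, so the condition fails.
- No to item 4 with unknown/not measured at 8b and 8c suggests that none was obtained. The same answers would arise if CSF was taken and no result was recorded.
- No at 8b usually points to a cell count having been done. But 8b sits in a list of signs present at admission or diagnosis, and it could be answered No where no count was made.
- Unknown to item 4, with nothing at 8b or 8c, leaves the matter open.

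An ambiguous infant with the temperature criterion and four or more signs could be placed in Level 3b wrongly, or left out of it wrongly.

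**The case against.** The best defence is that the intent is plain from the form itself. Item 4b speaks of a pathogen, and the following items offer every class of organism. A sample tested for bacteria together with other organisms is a truthful Yes. Training and completion guidelines (Sections 8.2 and 8.7) and a manual of study procedures (Section 4.9) are planned, and they may tell sites how to read 4a. That limits how often the problem would arise. It does not remove it, because the skip is part of the form and the guidance is not in the Protocol.

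A reader might go further than the documents allow in three ways:

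- *Level 1 bloodstream infection cannot be established.* It can, by its main route, for any recognised pathogen in a sample tested for bacteria.
- *The form records no timing for cultures.* It records the date of each positive sample, and the repeat block takes a second one. Only same-day pairs fail.
- *A lumbar puncture with only a cell count would be mistaken for no puncture, so Level 3b is unusable.* Item 8b records pleocytosis, and a completed count should show there as Yes or No. What remains is the narrower ambiguity set out above.

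It is also fair to say that a lost Level 1 usually costs a level and not classification, so the primary outcome is largely protected.

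**Conclusion.** The point holds for item 4a: as worded, it excludes a case tested only for virus or fungus from Level 1, against the definition and against the rest of the same form. Two lesser gaps also hold. Same-day cultures of a normally non-pathogenic organism cannot be checked against the two-culture rule, and the entry condition for meningitis Level 3b is inferred from items 4, 8b and 8c.

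The effect is on the distribution by level and the missing-element tables, with a marginal effect on applicability. It cannot be quantified, because the documents give no frequency of viral- or fungal-only testing, same-day repeat cultures, or CSF taken without a recorded result. The conclusion assumes that sites follow 4a and its skip literally and that no study manual overrides them.

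**What to change.** 1. In bloodstream item 4a, replace the word bacteria with pathogens (bacteria, fungi, viruses, protozoa), keeping the skip. This is a one-word correction plus a bracket, at almost no cost.
2. For repeat positive blood cultures, add draw time and draw site, each with Unknown allowed.
3. On the meningitis form, before item 4, add *Was a CSF sample obtained? Yes / No / Unknown*, and use that answer for the Level 3b entry condition.

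The cost is a few short fields and a form amendment; version 3.0 already added four data points, so there is precedent. The new fields may often come back Unknown. Section 4.1 reports that data generated at sites may not be recorded or retrievable, and the sources named in Sections 4.8 and 8.3 do not mention laboratory slips. Section 10 places case identification from May 2019 and version 3.0 is dated 1 November 2019. If entry has begun when the change is made, bloodstream forms with 4a answered No or Unknown should be queried again, so that the wording does not change part-way through the data.

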| 
a See list of pathogens and non-pathogens in Appendix 1.
 
b Sterile site: blood, sterile urine (catheter urine or supra-pubic aspirate), pleural fluid, ascitic fluid, broncho-alveolar lavage, bone biopsy, synovial fluid.
 
d Definitions: Apnea: pause in breathing <math>> 20</math> s; CRP or calcitonin levels above the local normal standards; Tachypnea/fast breathing: respiratory rate <math>> 60</math> breaths per minute; Tachycardia: heart rate <math>> 180</math> beats per minute; Bradycardia: heart rate <math>< 100</math> beats per minute; c Poor perfusion: CRT <math>> 2</math>. d <math>4000</math> or <math>> 20,000 \times 10^9</math> cells/L; Low Platelets/Thrombocytopenia: <math>< 100,000 \times 10^9</math>/L; Metabolic acidosis: <math>< -10</math> mmol/L (<math>-10</math> mEq/L)
 
e Increased according to locally defined and validated reference ranges.
 
f Also refer to Brighton collaboration case definition for fever [23].
 |                                                                                                                                                                                                                                                                                                                                                                                                                                                                                                                                                                                                                                                                                                                                                                                                                                                                                                                                                                                                             |                                                                                                                                                                                                                                                                                                                                                                                                                                                                             |

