| 6q | Abnormal platelet count ( Low Platelets/Thrombocytopenia: <100,000 × 10^9/L )                        | Yes
No
Unknown or not measured |
| 6r | Increased inflammatory markers (CRP, procalcitonin) ( CRP or calcitonin levels above the local normal standards ) | Yes
No                            |

|    |                                                                                |                                      |
|----|--------------------------------------------------------------------------------|--------------------------------------|
|    |                                                                                | Unknown or not measured              |
| 6s | Metabolic acidosis as defined by a base excess ( $<-10$ mmol/L ( $-10$ mEq/L)) | Yes
No
Unknown or not measured |
| 6t | Tachypnea ( respiratory rate <math>>60</math> breaths per minute )   | Yes
No
Unknown or not measured |
| 6u | Severe chest indrawing                                                         | Yes
No
Unknown                 |
| 6v | Grunting                                                                       | Yes
No
Unknown                 |
| 6w | Cyanosis                                                                       | Yes
No
Unknown                 |
| 6x | Change in level of activity                                                    | Yes
No
Unknown                 |
| 6y | History of convulsions                                                         | Yes
No
Unknown                 |

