### Congenital microcephaly (post-natally diagnosed)

#### POST NATALLY DIAGNOSED CONGENITAL MICROCEPHALLY

Small for gestational age is defined as a birth weight for gestational age below the 10th percentile based on a sex-specific reference population (WHO, 1995)

| Newborn case number                                                             |                                                                                     |
|---------------------------------------------------------------------------------|-------------------------------------------------------------------------------------|
| QUESTION                                                                        | INSTRUCTIONS                                                                        |
| PART 1 - GA and sex                                                      |                                                                                     |
| 1 Did a live birth, stillbirth, or spontaneous/therapeutic abortion take place? | Live birth
Stillbirth
Spontaneous abortion
Therapeutic abortion
Unknown |
| 2 What is the sex of the baby?                                                  | Male                                                                                |

|                                         |                                                                                                                                                                 |                                                                                                                                                                                                                                                                       |
|-----------------------------------------|-----------------------------------------------------------------------------------------------------------------------------------------------------------------|-----------------------------------------------------------------------------------------------------------------------------------------------------------------------------------------------------------------------------------------------------------------------|

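### The bloodstream-infection form and Annex III print a low-platelet cut-off that no blood count can exceed, so on a literal reading every measured count scores a Level 2 criterion

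*Protocol*

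**What the plan says.** Annex V, Neonatal invasive bloodstream infection, item 6q asks for Yes, No or Unknown on an abnormal platelet count and gives the meaning as "Low Platelets/Thrombocytopenia: <100,000 × 10 9 /L". Footnote d to the bloodstream-infection table in Annex III prints the same number and unit after "Low Platelets/Thrombocytopenia". The upper white-cell limit in that footnote has the same unit pattern: "> 20,000 \times 10^9 cells/L". Item 6p, on white cells, prints no count limits.

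In the Annex III table, "Abnormal platelet count d" is one of ten criterion lines for Level 2, which needs "3 or more criteria". For an organism normally considered non-pathogenic, Level 1 needs two positive cultures "PLUS 1 of the criteria as per level 2 of evidence". Platelets are not among the five Level 3 lines, of which two are needed.

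Protocol section 4.10 has cases classified by an automated tool. Section 5.5 has data analysed as entered in the eCRFs, without imputation. The form has no field for the platelet value.

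Two smaller slips sit in the same annex. The post-natal microcephaly form carries as its case definition "Small for gestational age is defined as a birth weight for gestational age below the 10th percentile", which is the text of the small-for-gestational-age form. Items 6r and 10o ask about procalcitonin but explain it as calcitonin.

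**The concern.** A cut-off that nothing can exceed does not discriminate. If site staff set a laboratory report in 10^9/L against the printed figure, every infant with a platelet count is recorded as abnormal. The stored answer is only Yes, No or Unknown, so a range check cannot catch a wrong Yes and the central team cannot recompute it.

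The answer feeds classification directly. At stake are:
- the distribution of levels for neonatal infection (section 5.3.1.1);
- for a narrower group of infants, whether a case is classified at all. That enters the applicability proportion (5.2.2.1), the comparison by factors (5.3.2) and the number of classified cases behind the minimum detectable odds ratio (5.2.1).

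**Working it through.** **Units.** The plan has no design figure to reproduce here; the check is a conversion of the printed threshold.

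- Printed: 100,000 × 10^9/L = 10^14/L = 10^8 per microlitre.
- Plausibility: at an assumed platelet volume of 5 to 12 fL, 10^14 platelets would occupy 10^14 × 5 × 10^-15 = 0.5 L to 10^14 × 12 × 10^-15 = 1.2 L in each litre of blood. No real count gets there.
- Assumed test counts of 50, 150, 450, 1000 and 2000 × 10^9/L all fall below the printed figure.
- If the numeral was meant per microlitre (an assumption; the protocol does not say so), 100,000 per microlitre = 100 × 10^9/L. The printed threshold is then 100,000 / 100 = 1000 times too high, and only the first of the five test counts lies below the converted value.

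That the printed value is impossible does not depend on the per-microlitre assumption; the factor of 1000 does.

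**Who changes class if 6q is always Yes when measured.** These are infants whose true platelet status is not low.

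- Exactly two other Level 2 lines, and Level 3 met: moves from Level 3 to Level 2. Still classified, so any-level proportions do not change.
- Exactly two other Level 2 lines, and Level 3 not met: moves from unclassified to Level 2. Example: tachycardia and pallor only, neither of which is a Level 3 line.
- Non-pathogenic organism in two qualifying cultures and no other Level 2 line: the platelet item alone completes Level 1.
- Three or more other Level 2 lines: Level 2 is reached without the platelet item.

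**Illustrative size.** Assume that each of the ten Level 2 lines is present independently with the same probability p. These are assumptions, not figures from the protocol.

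- Correct item: P(at least 3 of 10).
- Item always Yes: P(at least 2 of the other 9).
- The difference is (1 − p) × P(exactly 2 of 9), that is, infants two short of nothing but the platelet line who do not truly have low platelets.

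| p | Correct item | Always Yes | Gain |
|---|---|---|---|
| 0.1 | 0.070 | 0.225 | 0.155 |
| 0.2 | 0.322 | 0.564 | 0.242 |
| 0.3 | 0.617 | 0.804 | 0.187 |
| 0.4 | 0.833 | 0.929 | 0.096 |

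Check at p = 0.2: P(exactly 2 of 9) = 36 × 0.2² × 0.8⁷ = 0.302, and 0.8 × 0.302 = 0.242.

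The table concerns the Level 2 count only, among infants with a measured platelet count. It ignores that Level 2 applies only to infants who do not meet Level 1.

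**Microcephaly form.** Section 4.7.1 defines the outcome by head circumference; the form's header defines small for gestational age. The questions below the header still collect sex, gestational age, head circumference, its unit and its timing. The header can mislead a reader but changes no classification input.

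**The case against.** The strongest reply is that few staff will apply the printed number literally. The item is labelled as an abnormal platelet count with thrombocytopenia named beside it. Someone holding a report per microlitre and comparing it with 100,000, or following a laboratory flag, would not be misled. This stands: a reader might infer that every tested infant will be recorded as Yes, but that follows only from a literal comparison with a report in 10^9/L. What remains is that sites may answer the same item in different ways.

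Four further inferences go beyond the documents:

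- *White cells as a second automatic criterion.* Item 6p shows staff no faulty count limit, and that they would consult footnote d is conjecture. Part of the footnote's white-cell text is also broken in the copy read here.
- *A general bias in the equipment comparison of 5.3.2.* That analysis uses the proportion classified at any level, as does 5.2.2.1. A move from Level 3 to Level 2 leaves both unchanged. Only infants who fail Level 3 and have exactly two other Level 2 lines enter, and their number cannot be derived from the protocol.
- *A larger jump, from 26% or 54%.* Those baselines are P(at least 3 of 9) at p = 0.2 and 0.3, which assume that no infant truly has low platelets. With all ten lines they are 32% and 62%.
- *An error that can never be repaired.* Sections 8.1 to 8.3 provide for queries and for source documents kept at sites. Repair is possible, but only through the sites.

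**Conclusion.** The point holds as a threshold printed in an impossible unit, in both the form and the definition that it copies. Because the item feeds automated classification and no value is stored, this is more than clerical. Read literally, it inflates Level 2, completes Level 1 for some infants with a non-pathogenic organism, and adds newly classified cases in one narrow group.

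The size in practice is uncertain. The rises from 32% to 56% and from 62% to 80% rest on independence, a common assumed probability of 0.2 or 0.3, and a literal reading by every site; they show scale and are not estimates. The main exposure is the level distribution for bloodstream infection, one of three forms within one of seven outcomes. The sample size in section 5.1 is not affected.

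The microcephaly header and the calcitonin gloss are genuine copy errors. A reader might infer that they misclassify cases, but the microcephaly questions collect the right data and the labels of 6r and 10o name procalcitonin, so they are editorial.

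**What to change.** - Reconcile the platelet and white-cell units in item 6q and Annex III footnote d against the source GAIA definition, and change form and annex together. If the numerals prove to be per microlitre, the platelet figure equals 100 × 10^9/L. The protocol alone cannot settle this.
- Print the reconciled white-cell limits in item 6p.
- Query existing Yes answers to 6p and 6q against the laboratory report, since they cannot be corrected centrally, and rerun the classification for any that change.
- Editorial: replace the header of the microcephaly form with the section 4.7.1 definition, and calcitonin with procalcitonin in 6r and 10o.

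The cost is label edits in the eCRF and annex, and a targeted round of site queries. No new data from mothers or infants are needed.
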